## 304 **Economic Evaluation**

305 An economic evaluation will be conducted in addition to this randomized controlled trial to determine  
306 the cost per pressure ulcer event avoided from a health system payer perspective. This will involve the  
307 compilation of information on device costs, operational and maintenance costs, human resource  
308 requirements, and costs of care associated with developing a pressure ulcer. The resulting cost per  
309 pressure ulcer event avoided will indicate the value-for-money for health systems associated with the  
310 ForeSite PT™ system.

311

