255 pressure ulceration as per the staging system developed by the National Pressure Ulcer Advisory Panel  
256 and other skin appearance changes described above. The research nurse will conduct the Braden Scale

Ethics ID number: REB13-0794

Study Title: Effectiveness of a pressure-sensing mattress system for reducing the risk of pressure ulcer formation  
by lowering interface pressure in vulnerable patient populations: Parallel-two-group randomized trial

PI: [name]

Version number/date: V2 01/04/2014

and the head-to-toe skin assessment a second time within 24 hours prior to their discharge date, or on the seventh day (whichever comes first).

The demographic information that will be collected include: sex, date of birth, and race. Information on medical history that will be collected include: Charlston comorbidity index; CBC, pre-albumin and albumin, creatinine, liver function test results (alkaline phosphatase, AST), C reactive protein (CRO), glycosylated hemoglobin, and body mass index (BMI). Patient history data that will be collected include reason(s) for admission/diagnoses, level of bed mobility, bladder management, bowel management, history of cancer and/or treatment, history of cardiovascular disease, history of renal failure, use of immunosuppressive medications, previous pressure ulcers, smoking history, and illicit drug use.

4. Total cost of per admission. This information will be used in determining the cost-effectiveness of the ForeSite PT™ system. This information will be accessed using the participant's personal health number after he or she has been discharged from the hospital.

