### **Sample size**

A total of 600 patients will be recruited from Unit 36, Unit 58, and the ICU will be enrolled in the trial, in order to randomize 300 patients to each of the intervention and control arms. Sample size estimates for the primary outcome indicate a need for 294 patients in each of the intervention and control arms. This is based on an estimated control group event rate of 30%, an intervention group rate of 20% (i.e., a 33% relative risk reduction), an alpha level of 0.05, and 80% power.

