## 291 **Analysis and Statistical Methods**

292 Subjects will be stratified by their pressure ulcer risk, as determined by their Braden Score.

293 Data analysis will involve use of Chi-square and/or Fisher exact tests for between-group (i.e.,  
294 intervention and control groups) comparisons of the primary outcome and the secondary outcomes, and  
295 the Wilcoxon rank sum test for between-group comparison of strategic shifting. Chi square and t-tests  
296 will be used to compare baseline characteristics between groups, and logistic regression will be used for  
297 adjusted analyses if there are notable between-group differences for important baseline characteristics.  
298 Correlation between pressure distribution (the study's primary endpoint) with the hard clinical outcome  
299 (pressure ulceration and pressure-related skin appearance changes) will also be explored.

300 Univariate statistics will be used to summarize changes in pressure distribution as per the interface  
301 pressure feedback provided by the ForeSite PT™ system.

302 Univariate statistics will be used to summarize close-ended survey data, while open-ended survey data  
303 will be thematically analyzed.

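### Total cost per admission is left under a chi-square/Fisher sentence that does not suit it and cannot supply the cost difference the economic ratio needs (minor)

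*Protocol*

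**What the plan says.** Three places in the protocol bear on this.

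- **Secondary Outcomes, item 4** reads "Total cost of per admission. This information will be used in determining the cost-effectiveness" of the system. The figure is to be retrieved for each participant after discharge.
- **Analysis and Statistical Methods** names chi-square or Fisher exact tests for between-group "comparisons of the primary outcome and the secondary outcomes". The same section reserves the Wilcoxon rank sum test for strategic shifting and t-tests for baseline characteristics. Logistic regression is for adjusted analyses, and univariate summaries with thematic analysis are for the surveys.
- **Economic Evaluation** sets out a cost per ulcer event avoided from the payer's perspective. It lists the kinds of cost to be compiled and says that the resulting cost per "pressure ulcer event avoided will indicate the value-for-money for health systems associated with the" device.

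The **Sample size** section is relevant to the ratio's denominator. It rests on the primary outcome, which the Outcomes section defines as a composite of interface pressure measurements, not on ulcers.

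**The concern.** Cost per admission is an amount of money, not a category. Read as written, the analysis section gives it a test for counts in a table. To apply that test someone would have to choose cut-points, and the protocol gives none. The result would say whether the arms differ in the share of patients above or below those cut-points. It would not say how much more or less an admission costs in one arm, which is the quantity a cost per event avoided is built from.

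Establishing cost-effectiveness is the fourth secondary objective, so the planned comparison of cost should be able to serve it. A second, smaller matter is that the ratio divides by an ulcer difference the trial was not sized to estimate. A reader shown the ratio alone could not see how well that difference is known.

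**Working it through.** **Step 1. Match each secondary outcome to the method named for it.**

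| Secondary outcome | Kind of data | Method in Analysis and Statistical Methods |
|---|---|---|
| 1. Skin and soft tissue composite | event / category | chi-square or Fisher; fits |
| 2. Provider survey | treatment-group patients only | univariate summaries, thematic analysis |
| 3. Patient survey | treatment group only | univariate summaries, thematic analysis |
| 4. Total cost per admission | continuous amount | only the chi-square/Fisher sentence reaches it |

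No other named method is assigned to cost. The Economic Evaluation section does not name a between-arm comparison of total cost per admission either.

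**Step 2. What the ratio needs.** Cost per ulcer event avoided = ΔC / ΔE. Here ΔC is mean cost per patient in the intervention arm minus that in the control arm, and ΔE is the control ulcer risk minus the intervention ulcer risk. A chi-square or Fisher test on categorised cost gives a p-value about proportions. It does not estimate ΔC.

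**Step 3. Reproduce the plan's own figure.** Inputs from Sample size: "estimated control group event rate of 30" per cent; "an intervention group rate of 20% (i.e., a 33% relative risk reduction"); "an alpha level of 0.05, and 80% power". Sidedness is not stated; two-sided is taken. With pooled variance under the null and no continuity correction:

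n = [1.960·√(2·0.25·0.75) + 0.8416·√(0.30·0.70 + 0.20·0.80)]² / 0.10²
= [1.2002 + 0.5119]² / 0.01 = 293.2, rounded up to 294.

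This matches the stated "294 patients in each of the intervention and control arms". The plan is to "randomize 300 patients to each of the intervention and control arms", which gives power of 80.9% for 30% against 20% on the primary outcome.

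**Step 4. How well the same trial would estimate ΔE.** The protocol gives no ulcer rate, so the control rate p is an assumption, shown over a range. The intervention rate is taken as 2p/3, borrowing the one-third reduction from Sample size. At 300 per arm:

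SE = √[p_c(1 − p_c)/300 + p_t(1 − p_t)/300]; expected 95% CI = ΔE ± 1.96·SE.

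Example at 15%: SE = √[(0.1275 + 0.0900)/300] = 0.0269; 0.050 ± 0.0528 = −0.003 to 0.103.

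The last two columns come from 400,000 simulated trials per row.

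| Assumed control rate | ΔE | Expected 95% CI | Trials whose CI includes 0 | Trials with observed ΔE ≤ 0 |
|---|---|---|---|---|
| 30% | 0.100 | 0.031 to 0.169 | 19% | 0.3% |
| 20% | 0.067 | 0.007 to 0.126 | 40% | 1.6% |
| 15% | 0.050 | −0.003 to 0.103 | 54% | 3.6% |
| 10% | 0.033 | −0.011 to 0.078 | 68% | 8% |
| 5% | 0.017 | −0.015 to 0.049 | 83% | 18% |
| 2% | 0.007 | −0.014 to 0.027 | 91% | 31% |

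The expected interval excludes zero at 20% and 30% and includes it at 15% and below. Whether the denominator is well separated from zero therefore depends on a rate the protocol does not state.

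**The case against.** The strongest reply is that the chi-square/Fisher sentence is a blanket statement never meant to govern cost. The surveys are also secondary outcomes. They concern the system as used in the treatment group, so they cannot be compared between arms, and the same section handles them separately. Cost has a section of its own. This stands as far as intent goes: a reader might infer that the investigators will actually run a chi-square test on cost, or cut it at its median, and the protocol plans no such cut. What remains is that no sentence exempts cost and none names a suitable comparison, so the text needs correcting whatever was meant.

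Second, cost per event avoided is an ordinary summary measure, and the Economic Evaluation section is silent on intervals and sensitivity analysis rather than opposed to them. Such detail is commonly left to an analysis plan, which is not at hand. This stands, and the absence of an interval, a threshold or an acceptability curve is not counted as a fault here.

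Third, a reader might infer that the economic conclusion will be unbounded or wrong in sign. The protocol does not support that. At 30% against 20% the expected interval for the ulcer difference excludes zero and a reversed or null estimate is rare (0.3%). Reversal is the less likely result in every row of the table, and all the rates are assumed.

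Fourth, the Economic Evaluation section lists device, operating, staffing and ulcer-care costs and does not mention total cost per admission. The link between the two comes from Secondary Outcomes item 4. Some of those inputs are not described as patient-level, so a bootstrap applies to the cost retrieved per participant and not automatically to every component.

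**Conclusion.** The point holds as a minor correction. As written, the protocol places a continuous secondary outcome under tests for categorical data, and those tests would not produce the cost difference its own economic measure requires. The primary analysis, the sample size and the conduct of the trial are unaffected.

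The comment on the ratio is conditional. It rests on 300 per arm, a one-third relative reduction in ulcers and an assumed control ulcer rate. Under those assumptions the expected interval for the ulcer difference includes zero at control rates of 15% or lower, and single trials would give such an interval in 54% to 91% of cases over the range from 15% down to 2%. At 20% and 30% the figures are 40% and 19%. That is reason enough to show the ratio with its two components. It does not show that the ratio will mislead.

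**What to change.** In Analysis and Statistical Methods, exempt total cost per admission from the chi-square/Fisher sentence. State that mean cost per admission will be compared between arms as a difference in means with a patient-level bootstrap confidence interval.

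In Economic Evaluation, state that the incremental cost and the ulcer risk difference will be reported, each with its interval, beside the cost per ulcer event avoided. Say how total cost per admission combines with the listed device, operating, staffing and ulcer-care costs, so that the numerator is clear.

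The cost is a few sentences and slightly more analysis, using the per-participant cost and skin assessments already planned. The drawback is a headline less simple than a single ratio.
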